### Recruitment

The process of recruiting participants will be based on medical record review. All the hospitalized patients undergoing a kidney biopsy from September 2014 and the outpatients with a documented history of IgAN by kidney biopsy within 1 year will be screened according to the inclusion and exclusion criteria. There are 100 participating clinical centers and every center will need to enroll at least 12 patients.

### Randomization procedure, allocation concealment, implementation of blind method

Consecutive numbers are assigned to each participating center according to a center-stratified random order generated by SAS 9.4 Proc Plan. Peking University Clinical Research Institute takes the responsibility of generating the allocation sequence and an interactive voice-response or web-response system will be used to assign each patient a number and group. The centers then randomly assign patients to the AM or losartan potassium treatment group. The allocation ratio is 1:1. The test uses a double-dummy drug; therefore, in the whole course of the trial, the patients, the doctors and the statistical analysts of the trial are unaware of the treatments. In patients with SAEs, an emergency unblinding procedure will be initiated.

### Data collection and management

Table 1 gives an overview of assessment tests and the time of data collection. For each patient who is randomly assigned to a group, regardless of their final completion of the experiment, the baseline data and follow-up data will be saved. Patients enrolled in the trial will be treated preferentially and checked for free. The clinical investigators from each center collect the data and fill in the Case Report Forms. For keeping intact, first-hand data, we also design specified medical records for the clinical trial. Researchers write the medical records at the same time as making follow-up observations on the patients and ensure that the data records are timely, complete, accurate and true. The inspectors of the Venturepharm CRO Service Group will review the data. The inspectors are responsible for checking the consistency of all data sources, paper Case Report Forms and electronic databases. Original medical records and informed consents are archived in the participating centers and saved for at least 5 years after the clinical trials finish. The General Hospital of PLA is responsible for the establishment of network data registration platform, and investigators are responsible for the paper case report table entry to the platform. All data will be transferred to the data statistical units for data entry and management with the EpiData3.1 database.

### Statistical methods

The statistical analysis plan will be decided before database lock and unblinding of the trial. Statistical analysis for the trial will be performed by the Peking University Clinical Research Institute. Statistics software SAS 9.4 will be used for the data analysis. Data analysis follows the principles of intention-to-treat analysis (ITT). The full analysis set is defined as all randomly assigned patients with both a baseline and a post-baseline assessment. Last observation carried forward (LOCF) will be used to handle the missing data. Categorical variables are presented as counts with percentages and compared by the chi-square test or Fisher’s exact test. Continuous variables are presented as mean with standard deviation and compared by *t* test if the variables are normal distribution or Mann-Whitney *U* test if the variables are non-normally distributed. A *t* test (two independent samples) will be conducted to compare the primary and secondary outcomes. An analysis of covariance (ANCOVA) model for the primary outcome will be conducted considering baseline proteinuria and study center effect. The LS-means and 95% LS confidence intervals will be generated.

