### Trial design

This study is a multicenter, prospective, double-blind, double-dummy RCT. The study is designed as a noninferiority clinical trial. The hypothesis is that AM significantly reduces the urinary protein levels of IgAN patients and that its curative effect is not inferior to that of losartan potassium (100 mg/d) after 48 weeks of treatment. We have followed the Standardised Protocol Interventions: Recommendations for Interventional Trials (SPIRIT) 2013 Statement which defines standard protocol items for clinical trials [12]. See the items in Fig. 1 and Additional file 1 for the Checklist. The study protocol was designed by members of the Executive Committee (composed of the Department of Kidney Disease of Chinese People’s Liberation Army General Hospital, Peking University Clinical Research Institute). The protocol is being implemented by the study group comprising 100 clinical centers across China. The network database was designed by the Executive Committee. Venturepharm CRO Service Group which provides the clinical research associate service.

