### Eligibility, exclusion and exit criteria

The inclusion criteria are: (1) diagnosis of IgAN by kidney biopsy, (2) age 18 to 65 years, (3) blood pressure of ≤140/90 mmHg, (4) estimated glomerular filtration rate (eGFR) ≥45 ml/min/1.73 m^2^ (calculated with the use of the CKD-EPI Creatinine Equation 2009) [13], (5) 24-h proteinuria range of between 0.5 and 3.0 g, (6) agreement to participate and provision of signed informed consent. Additional file 2 shows the Informed Consent Form in more detail. The exclusion criteria are: (1) secondary IgAN, (2) allergy to AM or losartan potassium, (3) history of AM and ACE-I and/or ARB use within the last 6 months, (4) history of glucocorticoid, immunosuppressant, or *Tripterygium* drug use within the previous 1 year, (5) blood pressure of <90/60 mmHg, (6) serum potassium >5.5 mmol/L, (7) serum albumin <30 g/L, (8) unilateral or bilateral renal artery stenosis, (9) pregnant or lactating women, (10) severe heart, brain, liver, or hematopoietic system disease, or other serious illnesses that may affect survival, (11) participation in another clinical investigation. The exit criteria are: (1) endpoint event: proteinuria ≥3.5 g/24 h, doubling of serum creatinine, or receiving blood purification treatment, (2) blood pressure of >160/90 mmHg after antihypertensive drug combination therapy (convinced by measuring blood pressure three times within 2 weeks), (3) blood pressure of <90/60 mmHg after stopping using other antihypertensive agents, (4) serum potassium >5.5 mmol/L after antihyperkalemia drug treatment, (5) serum creatinine rapidly rising to >50% of the baseline within 4 weeks after treatment, (6) serious adverse events (SAEs): hospitalization (initial or prolonged), disability or permanent damage, life-threatening, death, congenital anomaly/birth defect and other serious events (important medical events) [14], (7) serious breach of protocol: participants failing to take medications according to protocol or taking some drugs that have a significant impact on the primary and secondary outcomes during the 48-week observation period, (8) loss to follow-up or withdrawal from the trial, (9) pregnancy during the trial.

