### Study outcomes

#### Primary and secondary outcome measure

The primary outcome is the change in 24-h proteinuria from baseline after 48 weeks of treatment. For this measurement, patients are instructed to collect urine over 24 h (from 07:00 to 07:00 the next day). Urine output and the total amount are measured and recorded. Twenty-four-hour urinary protein excretion is calculated based on the concentration and 24-h urine volume. The secondary outcome measures are the change in eGFR from baseline after 48 weeks treatment and the incidents of endpoint events (proteinuria ≥3.5 g/24 h, doubling of serum creatinine, or receiving blood purification treatment). All the urine and blood samples are delivered to the central laboratory within 4 weeks for testing.

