### Sample size

The sample size determination is based on the primary outcome 24-h proteinuria. The alpha level is set to a one-sided value of 0.025%. We assume that the expected decline of 24-h proteinuria is 1600 ± 500 mg. The noninferiority margin (0.5 of the estimated standard deviation) is 250 mg. With a 15% dropout rate, to enroll 124 patients per arm will offer 95% power to demonstrate noninferiority of AM compared to losartan with a 250-mg noninferiority margin. At the same time, based on the observation of safety, sample size expanded to 800 patients per arm will offer 80% power to detect the rare adverse reactions (incidence <0.5%) at least in one patient.

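### LOCF, the only missing-data method named for the week-48 noninferiority endpoint, has a bias of unknown direction that can push the false-noninferiority rate above 2.5%

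*Protocol article*

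**What the plan says.** Under Trial design the article states: "The study is designed as a noninferiority clinical trial". Under Primary and secondary outcome measure: "The primary outcome is the change in 24-h proteinuria from baseline after 48 weeks of treatment". Sample size gives a margin of 250 mg, an SD of 500 mg and 15% dropout. It arrives at 124 per arm for efficacy, then enlarges the trial to 800 per arm for safety.

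Statistical methods settles missing data in one sentence: "Last observation carried forward (LOCF) will be used to handle the missing data". No other method is named. The same section says "Data analysis follows the principles of intention-to-treat analysis (ITT)" and then "The full analysis set is defined as all randomly assigned patients with both a baseline and a post-baseline assessment".

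The exit criteria include high proteinuria, doubling of creatinine, "serum creatinine rapidly rising to >50% of the baseline within 4 weeks after treatment", low or uncontrolled blood pressure, persistent high potassium, serious adverse events and nonadherence. Proteinuria is measured at weeks 0, 4, 12, 24, 36 and 48, so a carried value comes from week 4, 12, 24 or 36.

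**The concern.** LOCF gives a patient who leaves at week 4 the week-4 value as the week-48 result. If the treatment effect is still developing, that value understates both the patient's response and the gap between the arms.

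In a superiority trial a shrunken gap usually costs power. In a noninferiority trial it makes an inferior treatment easier to pass, so the error that the one-sided level should control can rise. The Background lists the 24-week observation time of the previous trial as a limitation, yet LOCF puts measurements from week 36 or earlier back into the 48-week endpoint.

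Two features make this more than a technicality. The exit criteria tie leaving to outcome or to treatment effects, so the missing values are unlikely to be a random subset. And the enlargement for safety shrinks the standard error of the efficacy comparison, so a bias that would be minor at 124 per arm becomes large relative to the noise.

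**Working it through.** **Inputs from Sample size.** SD 500 mg, margin 250 mg, dropout 15%, power 95%, 124 per arm for efficacy, 800 per arm enrolled. The expected decline comes from "We assume that the expected decline of 24-h proteinuria is 1600 ± 500 mg". The level comes from "The alpha level is set to a one-sided value of 0.025", which the article prints with a percent sign after it.

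**The plan's own figure.** Per arm, n = 2 × (1.960 + 1.645)² × (500/250)² = 103.96, so 104, and 104/0.85 gives 123. The exact t-based calculation gives 105, and 105/0.85 = 123.5 gives 124, as stated. Only a level of 0.025 reproduces this. Read literally as 0.025%, the level would need 211, inflated to 249.

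**Standard error.** SE = 500 × √(2/n): 63.5 mg at 124 per arm and 25 mg at 800 per arm.

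**Equal dropout.** Set the true week-48 deficit of AM at the margin, 250 mg. Let a share d of each arm leave, carrying on average a fraction f of the final gap. Then:

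- Bias toward zero: b = 250 × d × (1 − f)
- One-sided error: 1 − Φ(1.96 − b/SE)

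With d = 0.15, and f assumed because the article gives no time course:

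| f | b (mg) | LOCF deficit (mg) | Error, 124 per arm | Error, 800 per arm |
|---|---|---|---|---|
| 0.50 | 18.75 | 231.25 | 4.8% | 11.3% |
| 0.75 | 9.375 | 240.625 | 3.5% | 5.6% |
| 1.00 | 0 | 250 | 2.5% | 2.5% |
| 1.25 | −9.375 | 259.375 | 1.8% | 1.0% |

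For f = 0.50 at 800 per arm: 18.75/25 = 0.75, and 1 − Φ(1.21) = 11.3%.

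**Unequal dropout.** The absolute decline on losartan, L, now matters. If response scales with f in both arms, the LOCF deficit is

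L × [1 − d_L(1 − f)] − (L − 250) × [1 − d_A(1 − f)]

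Take an assumed time course of 40/70/90/100% of the final effect at weeks 4/12/24/36, with leaving spread evenly over those visits. Then f = (0.40 + 0.70 + 0.90 + 1.00)/4 = 0.75. At 800 per arm:

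| L (mg) | Losartan / AM dropout | LOCF deficit (mg) | Error |
|---|---|---|---|
| 1600 | 20% / 10% | 1520 − 1316.25 = 203.75 | 46% |
| 600 | 20% / 10% | 570 − 341.25 = 228.75 | 13% |
| 1600 | 10% / 20% | 1560 − 1282.5 = 277.5 | 0.1% |
| 600 | 10% / 20% | 585 − 332.5 = 252.5 | 2.0% |

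The 1600 mg decline is the article's planning value; 600 mg is an assumed alternative.

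**Simulation check.** These formulas hold the SE at 25 mg. A simulation let it vary (3000 runs per scenario, correlation 0.6 between visits, slower course of 30/55/75/90/100%). At 800 per arm, with the range covering L = 1600 and 600 mg, the error was:

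- 15% dropout in each arm: 6.6% to 8.1%
- 20% losartan / 10% AM: 24% to 71%
- 10% losartan / 20% AM: 0 to 1.6%
- poor responders leaving, their bad value carried: 1.2% to 1.5%

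**The case against.** The strongest reply is that nothing in the article fixes the direction. A reader might infer that LOCF necessarily pulls the arms together and so favours noninferiority. The documents do not support that. More exits on AM, a gap that narrows by week 48, or poor responders leaving with a bad value carried forward all make LOCF conservative in the calculations above.

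Nor do the exit criteria show that losartan patients will leave more often. Low blood pressure and high potassium might fall more on losartan. But high proteinuria would fall more on AM if AM were truly worse, and uncontrolled blood pressure might fall more on the arm without active losartan. No exit rates by arm are given. This objection stands, and it limits the claim to possible inflation.

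A reader might also blame the post-baseline requirement for pulling the arms together. It does not do so by itself. It excludes randomised patients with no follow-up value, which is narrower than strict ITT, with a bias of unknown sign. Finally, the article names no per-protocol or missing-data sensitivity analysis, but it leaves the SAP to be settled before database lock, so their absence is not a fault here.

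The reply does not rescue LOCF as a stated rule. A method whose error rate depends so heavily on an unknown exit pattern does not secure the 2.5% level, even if some patterns make it conservative.

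**Conclusion.** The point holds as a risk to the error rate, not as a demonstrated bias in favour of AM. LOCF is fixed as the only named method for a primary noninferiority test with substantial, partly outcome-related dropout, and its bias can go either way.

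With equal 15% dropout at 800 per arm, the error is about 6% to 11% if leavers carry 75% to 50% of the final gap, and 1% if the gap later shrinks and they carry 125%. With unequal dropout it ranges from near 0 to well above 40%, driven largely by the assumed losartan decline. All these results place the true deficit at 250 mg with an SD of 500 mg; the time courses, the dropout split and the 600 mg decline are assumptions that the article neither gives nor rules out. Because the direction cannot be known in advance, the replacement should be fixed before unblinding.

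**What to change.** Replace LOCF as the primary method with a mixed model for repeated measures on the week 4, 12, 24, 36 and 48 values. Include treatment by visit, baseline by visit and centre, and test the week-48 contrast against the 250 mg margin. State that this model takes the place of the two-sample t test and the ANCOVA as the primary test.

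The model draws nothing from patients with no post-baseline value and assumes that leaving is explained by the recorded data. So support it with multiple imputation for all randomised patients, those without follow-up values included. Add a delta penalty to imputed AM values under the noninferiority null, raising imputed proteinuria by the margin. Keep LOCF only as a sensitivity analysis.

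The cost is protocol and SAP wording, more programming and possibly a slightly wider confidence interval. No new visits or measurements are needed, and the SAP was still open when the article was written.

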### Participant follow-up

The enrollment process includes a screening visit to assess eligibility and obtain the informed consent and collection of clinical and demographic information. After enrollment, participants are evaluated at visit 1 (baseline visit), visit 2 (4 weeks), visit 3 (12 weeks), visit 4 (24 weeks) and visit 5 (36 weeks) and visit 6 (48 weeks) with similar data collection as performed in the baseline visit (Table 1).

**Table 1 Tab1:** Study visits

Item	Screening visit	V1	V2	V3	V4	V5	V6
Visit							
Time	−1w	0w ± 7d	4w ± 7d	12w ± 7d	24w ± 7d	36w ± 7d	48w ± 7d
Confirm eligibility	√	√					
Written informed consent	√						
Clinical and demographic information	√	√					
Physical examination	√	√	√	√	√	√	√
Signs and symptoms	√	√	√	√	√	√	√
24-h urinary proteinuria	√	√	√	√	√	√	√
24-h urine creatinine	√	√	√	√	√	√	√
Routine urine test	√	√	√	√	√	√	√
Urine pregnancy test		√					
Routine blood test		√	√	√	√	√	√
Blood biochemical tests		√	√	√	√	√	√
eGFR	√	√	√	√	√	√	√
Serum cystatin C and high-sensitivity C-reactive protein		√			√		√
Electrocardiogram and		√					√
Chest X-ray examinations		√					√
Drug distribution		√	√	√	√	√	
Drug combination		√	√	√	√	√	√
Adverse event			√	√	√	√	√
Exit criteria assessment			√	√	√	√	√

Note: the urine pregnancy test is screened in fertile women aged from 18 to 50 years

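### Endpoint events are to be compared by methods that ignore time at risk, and one of the two tests the plan names, a t test, does not suit a binary event

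*Protocol article*

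**What the plan says.** All references are to the protocol article.

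- **Outcome.** Under Primary and secondary outcome measure, one secondary outcome is "the incidents of endpoint events (proteinuria ≥3.5 g/24 h, doubling of serum creatinine, or receiving blood purification treatment").
- **The event ends participation.** The exit list begins: "The exit criteria are: (1) endpoint event: proteinuria ≥3.5 g/24 h, doubling of serum creatinine, or receiving blood purification treatment". The other grounds for exit include blood pressure, potassium, a rapid creatinine rise within 4 weeks, serious adverse events, protocol breach, and "loss to follow-up or withdrawal from the trial".
- **Timing.** Post-baseline assessments are at "visit 2 (4 weeks), visit 3 (12 weeks), visit 4 (24 weeks) and visit 5 (36 weeks) and visit 6 (48 weeks"), and Table 1 schedules the check of exit criteria at each of them.
- **Analysis.** Statistical methods has a general rule: "Categorical variables are presented as counts with percentages and compared by the chi-square test" or Fisher's exact test. A separate sentence prescribes a two-sample t test for the primary and secondary outcomes alike. Missing data are filled by LOCF. The full analysis set needs a baseline and a post-baseline assessment.
- **Dropout.** Sample size assumes it at 15% ("With a 15% dropout rate, to enroll 124 patients per arm will offer 95% power"), for the primary outcome and without a split by arm. No event rate is given for the endpoint events.

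**The concern.** The endpoint event has a date, and the patient stops being at risk when it occurs or when he or she leaves for another reason. Neither stated test uses that information. The two sentences also conflict: the general one implies percentages with chi-square or Fisher, while the one that covers secondary outcomes by name gives a t test, which does not suit a yes/no outcome. Resolving that conflict in favour of chi-square would still leave follow-up time ignored.

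Two things are at stake. First, the reported percentage understates the 48-week risk. Second, if patients leave one arm earlier or more often than the other, the arm with less follow-up appears to have fewer events. Unequal exit is possible here because one arm receives an active angiotensin-receptor blocker and the other does not, and several exit criteria (blood pressure, potassium, creatinine) could respond to that difference. The documents do not say that it will happen.

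**Working it through.** **The plan's own figure.** The only related figure is 124 per arm for the primary outcome. With SD 500 mg, margin 250 mg, 95% power and one-sided alpha 0.025: n = 2 × (1.960 + 1.645)² × 500²/250² ≈ 104, and 104/0.85 gives 123. The t-based n is 105, and 105/0.85 gives 124. The figure reproduces (with alpha read as 0.025, not the printed 0.025%). It supplies the 15% dropout used below but says nothing about the endpoint events.

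**Who counts as event-free.** This follows from two stated rules read together.
- No post-baseline assessment: outside the full analysis set, so excluded.
- At least one post-baseline assessment, no event, then leaves: in the set, and LOCF carries the event-free status to week 48.

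**Size.** Assumptions: constant event hazard, dropout independent of the event, true 48-week risk p = 10%. Write λ = −ln(1 − p) = 0.1054, with time as a fraction of 48 weeks.

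*Version A: dropout d spread evenly over 48 weeks, everyone in the denominator.*

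Crude proportion = (1 − d)p + d × [1 − (1 − e^−λ)/λ] = (1 − d) × 0.10 + d × 0.0509

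- d = 10%: 0.0951
- d = 15%: 0.0926
- d = 20%: 0.0902
- ratio for 20% v 10%: 0.0902/0.0951 = 0.948

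*Version B: constant dropout hazard θ = −ln(1 − d), events detected only at the five visits, full analysis set as denominator.*

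Crude proportion = Σ[e^(−λv₍k−1₎) − e^(−λv₍k₎)] × e^(−θv₍k₎) ÷ e^(−θv₁), with v = 4/48, 12/48, 24/48, 36/48, 1

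For d = 15%:
- event increments: 0.0087, 0.0173, 0.0253, 0.0247, 0.0240
- share still attending: 0.9865, 0.9602, 0.9220, 0.8852, 0.8500
- sum of products: 0.0908; divided by 0.9865 this gives 0.0920
- excluded for lack of any post-baseline visit: 1 − 0.9865 = 1.35%

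For d = 10% and 20%: 0.0947 and 0.0893, ratio 0.942.

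**Error rates and power.** Version B was simulated with 800 per arm, 3,000 trials per scenario and a two-sided 5% test.

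| True risk | Dropout | Crude % | Chi-square rejects | Log-rank rejects |
|---|---|---|---|---|
| 10% v 10% | 15% v 15% | 9.2 v 9.2 | 5.0% | 5.1% |
| 10% v 10% | 10% v 20% | 9.5 v 8.9 | 7.0% | 5.5% |
| 10% v 10% | 5% v 25% | 9.8 v 8.6 | 12.2% | 5.1% |
| 5% v 5% | 10% v 20% | 4.7 v 4.4 | 5.7% | 5.1% |
| 10% v 6% | 15% v 15% | 9.2 v 5.5 | 80.3% | 80.5% |

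The simulation standard error near 5% is √(0.05 × 0.95/3000) = 0.4 percentage points. Kaplan-Meier recovered 10.0% in each arm when the true risk was 10% and dropout was 15% v 15% or 10% v 20%.

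**Where precision comes from.** A separate illustrative simulation of the proteinuria component (400 runs, 800 per arm, 15% dropout, event rates about 5% v 3%) gave power of 72% for chi-square, 71% for unadjusted Cox and 80% for Cox with log baseline proteinuria. Timing added nothing; the covariate did.

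**The case against.** The strongest reply is that a statistical analysis plan is promised before database lock, and that an article may leave the model for a secondary outcome to it. Silence about survival methods would indeed be no finding. But Statistical methods is not silent: it names the tests, the missing-data rule and the analysis set, and the point concerns those choices.

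A second reply is that planned follow-up is 48 weeks for everyone, so a proportion is a legitimate target. That is fair when follow-up is complete. The plan itself expects dropout and lists many grounds for exit, and LOCF then treats partial follow-up as complete.

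Several stronger readings are tempting and are not supported:

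- *All patients lost early count as event-free.* Those without a post-baseline assessment are excluded. Carrying the others forward is inferred from LOCF and the analysis set; it is not written as a rule for events.
- *The 15% dropout biases the comparison of arms.* It does not if balanced. It is a planning figure, and no arm-specific rate is given.
- *The ratio could be 0.90.* That needs every dropout (20% v 10%) to leave at week 4 and to have completed that visit. Patients who leave before it are outside the set.
- *Using event timing gains power.* It does not, as shown above. A binary regression could use the baseline covariate too.
- *A survival analysis removes the bias.* Only if censoring is independent given baseline. A patient removed for a rapid creatinine rise may have been on the way to doubling, so censoring there may be informative.

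**Conclusion.** The point holds in a limited form. For an outcome that ends follow-up and is assessed at five visits, the plan names two incompatible tests. One is unsuited to a binary event and neither accounts for time at risk.

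With 15% independent dropout, a 10% risk is reported as 9.2–9.3%. Balanced dropout leaves the ratio, the error rate and power essentially unchanged. The comparison is distorted only if dropout differs by arm: at 10% v 20% and a true risk of 10% in both arms, the crude ratio is 0.94–0.95 and the chi-square error rate about 7%, against about 5% for log-rank. At a 5% risk the error rate is 5.7%.

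The event risks, the split by arm, constant hazards and independent dropout are all assumptions. The outcome is secondary, and nothing here affects the noninferiority test on proteinuria. The change is worth making because it is cheap and the present text contradicts itself.

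**What to change.** In Statistical methods:

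1. Remove endpoint events from the t-test sentence.
2. Analyse them as time from randomization to first event, using a discrete-time model for the five visits or a Cox model, with treatment and log baseline proteinuria. Report the hazard ratio with its 95% confidence interval.
3. Give Kaplan-Meier 48-week risks by arm.
4. Censor event-free patients at their last assessment, and state that LOCF does not apply to this outcome.
5. Keep counts and percentages as description only.
6. Add a sensitivity analysis for early exits that may be related to treatment or to the outcome. For example, count exits for rapid creatinine rise as events, and tabulate reasons and times of exit by arm.

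**Cost.** Plan wording and a few lines of SAS. Visit timing and baseline proteinuria are already scheduled in Table 1, so no new data or patients are needed. The downside is that the main result becomes a hazard ratio that relies on censoring being independent given baseline. Any gain in precision should be attributed to the baseline covariate, not to event timing.

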**Methods:**

We will conduct a multicenter, prospective, double-blind, double-dummy randomized controlled study. The study is designed as a noninferiority clinical trial. Approximately 1600 biopsy-proven IgAN patients will be enrolled at 100 centers in China and followed up for as long as 48 weeks. IgAN patients will be randomized assigned to the *Abelmoschus manihot* group (in the form of a *huangkui* capsule, 2.5 g, three times per day) and the losartan potassium group (losartan potassium, 100 mg/d). The primary outcome is the change in 24-h proteinuria from baseline after 48 weeks of treatment. Change in estimated glomerular filtration rate (eGFR) from baseline after 48 weeks of treatment, the incidence of endpoint events (proteinuria ≥3.5 g/24 h, the doubling of serum creatinine, or receiving blood purification treatment) are the secondary outcomes. Twenty-four-hour proteinuria and eGFR are measured at 0, 4, 12, 24, 36 and 48 weeks.

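### Two 24-h proteinuria collections are scheduled before dosing, but the ANCOVA for the primary outcome, as naturally read, adjusts for only one; entering both is an optional, free gain in precision

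*Protocol article*

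**What the plan says.** The endpoint, under Primary and secondary outcome measure, is a change score: "The primary outcome is the change in 24-h proteinuria from baseline after 48 weeks of treatment". Statistical methods lists a two-sample t test for the primary and secondary outcomes and then adds: "An analysis of covariance (ANCOVA) model for the primary outcome will be conducted considering baseline proteinuria and study center effect". It ranks neither analysis above the other, and it does not say how many readings make up the baseline covariate. It leaves the analysis plan to be settled before database lock.

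In Table 1 (Participant follow-up), the row "24-h urinary proteinuria" is ticked at screening (-1w) and at V1 (0w), as well as at every later visit. Drug distribution is first ticked at V1. The accompanying text says that "participants are evaluated at visit 1 (baseline visit", and the abstract lists measurement from week 0: "Twenty-four-hour proteinuria and eGFR are measured at 0, 4, 12, 24, 36 and 48 weeks". The eligibility section excludes patients with a "history of AM and ACE-I and/or ARB use within the last 6 months", so both early collections fall in a period free of either trial treatment. The entry window is a "24-h proteinuria range of between 0.5 and 3.0 g".

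**The concern.** A 24-h urine protein value is an imperfect measure of a patient's usual excretion. The noisier the baseline covariate, the less of the week-48 variance it explains and the wider the adjusted interval. A second reading taken about a week earlier, also off trial treatment, carries further information on the same quantity. If the model uses only the visit 1 value, information already collected on every screened patient goes unused. What is at stake is the width of the interval for the between-arm difference in proteinuria, and nothing more.

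**Working it through.** **Inputs from the article (Sample size).** SD 500 mg, noninferiority margin 250 mg, 95% power, 15% dropout, 124 per arm for efficacy, 800 per arm enrolled for safety. Alpha is taken as one-sided 0.025. It is printed with a percent sign, but read literally it would give 249 per arm rather than 124.

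**Reproducing the stated figure.** n = 2 × (1.960 + 1.645)² × 500² / 250² = 104 per arm, and 104 / 0.85 gives 123. The exact noncentral-t calculation gives 105, and 105 / 0.85 gives 124. The plan's figure holds.

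**Precision at the planned size.** Completers: 800 × 0.85 = 680 per arm. With no baseline adjustment, SE = 500 × √(2/680) = 27.1 mg and the 95% half-width is 1.96 × 27.1 = 53.1 mg. The margin is 250 / 27.1 = 9.2 standard errors. Power exceeds 99.99% if the arms are truly equal, and is 99.98% if *Abelmoschus manihot* is truly 100 mg worse.

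**Effect of a second pre-dose value.** Let ρ be the correlation of either pre-dose value with week 48, and r the correlation between the two pre-dose values. The article gives neither, so both are assumed.
- One baseline covariate: residual variance is proportional to 1 − ρ².
- Two baseline covariates: proportional to 1 − 2ρ²/(1 + r).

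To convert to milligrams, take 500 mg as the SD of change and equal variances at baseline and week 48. The SD of a single reading is then 500/√(2(1 − ρ)). Half-widths use 680 per arm.

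| ρ | r | Residual variance (share), one → two | Reduction | Half-width, one → two (mg) |
|---|---|---|---|---|
| 0.3 | 0.9 | 0.910 → 0.905 | 0.5% | 42.8 → 42.7 |
| 0.5 | 0.8 | 0.750 → 0.722 | 3.7% | 46.0 → 45.2 |
| 0.6 | 0.8 | 0.640 → 0.600 | 6.2% | 47.5 → 46.0 |
| 0.5 | 0.5 | 0.750 → 0.667 | 11% | 46.0 → 43.4 |
| 0.6 | 0.6 | 0.640 → 0.550 | 14% | 47.5 → 44.1 |
| 0.7 | 0.7 | 0.510 → 0.424 | 17% | 49.0 → 44.7 |
| 0.8 | 0.8 | 0.360 → 0.289 | 20% | 50.4 → 45.2 |

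Example, last row: SD of a reading = 500/√0.4 = 791 mg. Residual SD falls from 791 × √0.360 = 474 to 791 × √0.289 = 425 mg. Half-width falls from 1.96 × 474 × √(2/680) = 50.4 to 45.2 mg.

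The equal-correlation rows are the favourable end. They suppose that two off-drug collections a week apart agree no better with each other than with a collection taken 48 weeks later on treatment. When r exceeds ρ, the gain shrinks, as the first three rows show.

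**The case against.** The strongest reply is that nothing here is stated wrongly. That the covariate is a single value is inferred from visit 1 being called the baseline visit. Statistical methods does not fix it, and deriving a baseline is ordinarily a matter for the analysis plan. This stands: the point is a suggestion for that plan, not an error in the protocol.

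The second reply is that the gain does not matter here. Enrollment is more than six times the efficacy requirement (800 / 124 = 6.5), and the half-width is far inside the margin with or without adjustment. This also stands for the noninferiority verdict. It does not remove the case for a slightly tighter estimate at almost no cost.

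Several stronger readings are tempting, and the article does not support them:
- *The plan's primary analysis is inefficient.* The ANCOVA is not named as primary. The unadjusted t test listed beside it uses no covariate, so the gain applies only to the ANCOVA.
- *Proteinuria is the only covariate.* Center is also in the model.
- *Error in the subtracted baseline passes into the result.* With the visit 1 value as a covariate, analysing the change or the week-48 value gives the same treatment estimate and standard error.
- *Regression to the mean from the entry window distorts the comparison.* It acts on both randomized arms alike and does not bias the contrast.
- *Screening serves only for eligibility.* Table 1 ticks the eligibility check at both screening and visit 1.
- *The second value is worth 12.5-25% more patients.* This follows from the equal-correlation rows (0.750/0.667 = 1.125; 0.360/0.289 = 1.25) and is therefore a best case.

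**Conclusion.** The point holds as an optional improvement. Two pre-dose collections are scheduled, and the ANCOVA as naturally read uses one. Using both lowers residual variance by about 0.5% at the unfavourable extreme, 4-6% in the middle range and up to 11-20% if all correlations are equal. At the stated SD of 500 mg and 680 completers per arm, this shortens the half-width by roughly 1-5 mg, and by about 0.1 mg at the unfavourable extreme. It does not materially change power at 250 mg and it corrects no bias.

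This rests on assumed correlations, equal variances at baseline and week 48, 500 mg being the SD of change, and the visit 1 collection being completed before the first dose, as the order of Table 1 suggests.

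**What to change.** In the ANCOVA for the primary outcome, enter the screening and visit 1 24-h proteinuria values as two separate covariates alongside center. Prespecify a rule for a missing screening value, for example imputation from other baseline data without regard to arm.

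Separate covariates are safer than a plain mean. Samples may take up to 4 weeks to reach the central laboratory, so the screening result may come from a local one (an inference; the article does not say). Two covariates remain valid in that case, and also if screening was the reading used for the entry window. The visit 1 value can stay as the one subtracted when change is described.

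The cost is one line in the analysis plan and one degree of freedom, with no added visit or sample. By the article's own timetable, it can be settled before database lock and unblinding.
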